#### Secondary outcome measures

• Acceptability and usefulness of three patient-completed questionnaires: a generic quality of life (QoL) questionnaire (EQ-5D), a validated disease-specific QoL questionnaire (ThyDQoL) and the disease-specific hypothyroid symptom checklist (ThySRQ). The time taken to complete the three questionnaires will be recorded and questionnaire completion rates will be calculated. Any third-party help used in a questionnaire’s completion will be recorded.

• Assessment of mobility and risk of falls in this population group as measured by the nurse-administered TUG and FRAT.

• Changes in specific cardiovascular risk factors (lipid profile (total cholesterol, high-density lipoprotein, triglycerides), blood pressure and body weight) and serum collagen type-1 cross-linked C-telopeptide (serum CTX).

#### Data collection and outcome assessments

The following procedures and assessments will be carried out in accordance with the study schedule shown in Table 1.

• Written informed consent.

• Randomization: Usual or reduced dose of LT4

• Participant-completed questionnaires: ThyDQoL, ThySRQ and EQ-5D. A private area will be provided for the participant to complete the questionnaires. If patients refuse to answer certain questions, their wishes will be respected. A record of start and finish times will be retained for patient-completed questionnaires.

• Nurse-administered questionnaires: FRAT and TUG

• Physical examination: Height, weight, blood pressure, pulse.

• Venepuncture: 5 to 10 mL blood (TSH, free thyroxine (FT4), free triiodothyronine (FT3), thyroid peroxidase antibodies, total cholesterol, high-density lipoprotein, triglycerides, CTX

• Clinical history: relevant medical history and medication list.

• Study medication dosing according to dose titration guidelines.

• Study medication compliance and concomitant medication checks.

• Clinical history: adverse events, serious adverse events, changes to concomitant medication.

• Assess integrity of the blind by asking the participant: ‘It is important for the interpretation of the results of the study that we ask you the following: “Do you think you were taking your usual or a lower dose of LT4? Why do you think this?”’

#### Data handling and record keeping

Medical information obtained at each visit will be recorded in the subject’s medical notes or other source documentation in real time. Data will be collected on paper case report forms and entered by an authorized member of the research study team on a secure validated clinical data management system. Data will be entered either at Bensham Hospital (for visits conducted at Bensham or at the participant’s home address) or at the Clinical Research Facility (for visits conducted at the RVI). The clinical data management system will be web-based, allowing access for authorized staff at Newcastle upon Tyne Hospitals NHS Foundation Trust, Gateshead Health NHS Foundation Trust and Newcastle University via password protection. Data will be handled, computerized and stored in accordance with the Data Protection Act 1998. No participant-identifiable data will leave the study site (the case report forms will identify participants by initials, date of birth and unique patient number only). Strict confidentiality will be ensured while dealing with patient-sensitive data in accordance with the Caldicott Guardian’s recommendations (applications will be made to the relevant Caldicott Guardian for use of NHS patient data).

All study data will be held in strict confidence by the investigators and research team. Data and documents will be stored in locked cupboards. A confidential list of trial identifiers and corresponding patient-identifying details will be held at site in a locked cupboard by the principal investigator. The quality and retention of study data will be the responsibility of the chief investigator. All study data will be retained in accordance with the latest Directive on Good Clinical Practice (2005/28/EC) and local policy.

#### Submission of accrual data to the UK Clinical Research Network

This study will apply for adoption to the NIHR Primary Care Research Network Portfolio. Accrual data will be submitted on a monthly basis, by Newcastle Clinical Trials Unit, in accordance with NIHR Clinical Research Network guidelines.

#### Study compliance and withdrawal

Compliance with study medication (IMP) will be assessed and documented by the research team by checking and recording the number of return capsules at each visit. This allows any issues to be addressed immediately with the participant. Compliance will be classed as good if between 80% and 100%.

Participants may withdraw from the study at any time without giving a reason. The investigator may also withdraw patients from the study drug in the event of inter-current illness, adverse events, serious adverse events, suspected unexpected serious adverse reactions, protocol violations or administrative or other reasons. Participants who withdraw will be asked if they would be willing to provide follow-up data collected as per the study protocol. Participants withdrawn from the study will not be replaced.

#### Pharmacovigilance

The safety of the lower dose of LT4 in this study will be evaluated by examining the occurrences of all adverse events, adverse drug reactions, unexpected adverse reactions, serious adverse reactions or suspected unexpected serious adverse reactions as defined by the Medicines for Human Use (Clinical Trials) Regulations [19]. The relationship and expectedness of the adverse event or reaction (causality) will be assessed by the site investigator and relayed to the chief investigator who, on behalf of the sponsor (Newcastle upon Tyne Hospitals NHS Foundation Trust), will notify the regulatory bodies, the Medicines and the Healthcare Products Regulatory Agency (MHRA) and the research ethics committee (REC), within 7 days for fatal and life-threatening events and 15 days for non-life-threatening events. All study investigators will be notified.

Most adverse events and adverse drug reactions that occur in this study, whether they are serious or not, will be expected treatment-related toxicities due to the drugs used in this study. A full summary of product characteristics of Eltroxin have been published [18].

We do not anticipate adverse effects for the lower dose of LT4. Although the current uniform serum TSH reference range of 0.4 to 4.0 is applied across all age groups, in real practice a significant proportion of individuals do have biochemical features of mild under-replacement, which goes unrecognized until a blood test is performed. If severe hypothyroidism develops (TSH >10 mU/L with low FT4 levels), then symptoms including fatigue, weight gain and poor memory may develop. We will assess the clinical impact of thyroid function via hypothyroid-specific symptom checklists, ThySRQ, and biochemically (TSH and FT4 levels) at 12 and 24 weeks to detect individuals who are unwittingly developing severe hypothyroidism. We will adjust their LT4 dose accordingly. Participants will also be provided with a helpline number in case they experience any problems.

#### Statistical analysis

As this is a feasibility study, the analyses of the data collected will be mainly descriptive, with 95% confidence intervals reported where appropriate. As well as patient blinding to treatment allocation, data analysis will also be blinded. At baseline the distribution of all numerical variables will be examined graphically and summarized by appropriate measures of location and spread. Similarly, baseline categorical variables will be tabulated and percentages reported.

#### Sample size calculation

No formal sample size calculation has been performed for the RCT component of this feasibility study as the primary outcome measures are concerned with the recruitment to and randomization of the trial and the acceptability of the trial in this population of patients. As this is a trial with 6 months follow-up, any investigation of changes in key study parameters from baseline to 6 months will only be exploratory. A sample size of *n* = 50 will provide sufficient data [14] to estimate the variability in the responses at baseline and assess the feasibility of the trial.

### SORTED B: qualitative study

#### Aim

The aim is to identify, describe and understand factors associated with participation of elderly people in the trial.

#### Objectives

The objectives are to explore the reasons for participation and non-participation in the RCT (SORTED A) amongst people aged 80 years and over with LT4-treated primary hypothyroidism; to examine the decision-making process of elderly people in choosing whether to participate in the RCT; to explore aspects of health and well-being with differing doses of LT4 replacement for primary hypothyroid disease and to explore issues around retaining elderly people in the RCT.

#### Design and method

In-depth interviews with key informants, 8 to 10 people, who have agreed to participate in the RCT (Group 1) and 6 to 8 people who did not wish to participate in the RCT (Group 2) will be conducted. Participants will be approached sequentially.

To understand participants’ experiences of the trial (*n* = 8 to 10), we will focus on their experience of the medication review (for example, the perceived impact on health and well-being, any fears or concerns and compliance issues) and their participation in the trial (for example, their acceptability of trial processes, changes or improvements they feel we could make and retention issues). We will interview them at approximately 2 weeks after randomization and up to 2 weeks after SORTED A visit 3 or trial termination whichever is sooner. These participants will be recruited to Group 1.

To explore the reasons why patients declined to take part in the RCT, we will focus on their understanding of the trial processes (for example, the information they were given, the encounter with the recruiter and their ideas and/or concerns about randomization and consent) and the intervention (willingness to have medication reviewed and/or changed, ideas and/or concerns about the effect of a dosage change on their health). These one-off interviews will take place within 2 weeks of participants declining to take part in the trial so as to minimize problems of information recall. These participants will be recruited to Group 2.

Participants will have the choice of being interviewed alone or with their significant others, either in their own homes or in an appropriate clinical setting.

#### Participant recruitment and consent

Potential Group 1 participants will be approached by a member of the central study team after they have provided written informed consent for the RCT. They will be provided with a study invitation pack consisting of an invitation letter, a participant information sheet and a consent form for SORTED B Group 1. Following their agreement to participate, the central study team will then contact potential participants by telephone 7 (+/− 3) days later to gauge the participants’ interest in taking part, to answer any initial questions and to arrange a convenient place, date and time for the interview.

Group 2 will be identified when potential participants return reply slips to the central team to indicate that they do not wish to participate in the RCT or when reply slips are not received within the specified 4-week period. This group is not identifiable to the central study team and we will require the relevant NIHR Primary Care Research Network research nurse, the general practice staff or the secondary care clinician responsible for the patients’ routine clinical care to approach this group. Each potential participant will be sent a SORTED B Group 2 invitation pack within 2 working days (after checking living status) consisting of an invitation letter, a participant information sheet, a consent form and a stamped addressed envelope for returning the reply slip to the central study team. For potential participants who do not respond to the initial RCT (SORTED A) invitation, the SORTED B Group 2 invitation pack will accompany the reminder letter for the RCT, minimizing the number of approaches to any particular patient.

For both groups, once initial agreement to participate is given, an interview will be arranged by the central study team either at the patient’s home or at Bensham Hospital. The participant and a friend or relative (if applicable) will be given an opportunity to ask questions. Written informed consent will be obtained.

A pre-screening log will be held by the recruiting GP surgery or hospital site, which will include the patient’s name and address and the date of the invitation letter. When reply slips of acceptance or refusal have been received by the site study staff, the recruiting practice or hospital site will be informed. If no reply is received, one repeat invitation pack will be sent to potential participants.

#### Results and analysis

Interviews will be conducted by the research nurse. The interviews will be semi-structured and the questions will be open ended, neutral and sensitive to capture the experiences of older people. All interviews will be audio-recorded with the respondent’s written consent, transcribed (and edited to ensure the anonymity of the respondent). The transcripts will form the data for the formal analysis. We will use QSR NVivo data collation and management software to assist in the coding of the data. Analysis will be conducted according to the standard procedures of rigorous qualitative analysis (open and focused coding, constant comparison, deviant case analysis and memoing) [20]. We will also conduct a series of ‘data analysis clinics’ where the research team will share and exchange interpretations of emerging and key issues [21].

### SORTED C: Retrospective cohort study

#### Aim

The aim is to collect the data required to inform a sample size calculation for SORTED II, the future full study where the primary outcome will be the 4-year all-cause mortality and cardiovascular morbidity.

#### Objectives

The objectives are to collect data to inform the design of the future full study, SORTED II. In particular, they are to estimate the distribution of the time-to-death variable for treated hypothyroid patients aged 80 years and over with 4 years of follow-up and to describe a number of other variables at study entry in 2008 for the cohort (time since diagnosis of hypothyroidism, time since LT4 treatment initiation, TSH level at diagnosis, FT4 level at diagnosis, cause of death (if applicable), age, gender, smoking status, body mass index, diabetes mellitus, hypertension and any other significant co-morbidities).

#### Design

This will be a retrospective cohort of 400 treated hypothyroid patients aged 80 years or more registered in 2008 in primary care practices.

#### Sample size

A total of 400 individuals who were 80 years or more in 2008 and were being treated for hypothyroidism will be analyzed. This will provide a 95% CI for the mortality rate in the population of interest with a width of at most ±5% to inform the power calculation for the full study.

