#### Sampling and participants

To identify patients for inclusion in the cohort study, the general practice will perform a database search of patient electronic records (Figure 1), which simultaneously identifies patients for SORTED A and C. Based on the information collected in the feasibility work and using an average practice list size of 7,000, we estimate that we need to recruit 20 general practices to achieve a sample size of at least 400 patients. In Northumberland, Tyne and Wear there are approximately 300 general practices of which 65 are GP research sites. The Primary Care Research Network staff will identify 20 practices to approach and will mail out the study literature. We do not anticipate a problem recruiting general practices to participate but if we cannot achieve our cohort of 400 patients from the first 20 general practices recruited, we will approach further practices.

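### SORTED C: the ±5% precision bound for 400 patients assumes independent patients, and sampling them through about 20 practices means it is not guaranteed

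*Protocol article*

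**What the plan says.** The Sample size section of SORTED C fixes the cohort: "A total of 400 individuals who were 80 years or more in 2008 and were being treated for hypothyroidism will be analyzed". The only reason given for that number is precision: "This will provide a 95% CI for the mortality rate in the population of interest with a width of at most ±5" per cent, with the result feeding the power calculation of the definitive trial. No condition is attached to the bound.

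The next section, Sampling and participants, says how the 400 are found. In each practice, "the general practice will perform a database search of patient electronic records", and from an average list size of 7,000 the authors estimate that "we need to recruit 20 general practices to achieve a sample size of at least 400 patients". The practices are not described as a random draw: "The Primary Care Research Network staff will identify 20 practices to approach". There is one contingency: "if we cannot achieve our cohort of 400 patients from the first 20 general practices recruited, we will approach further practices". It is triggered by a shortfall in patients, not by a loss of precision.

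The SORTED C sections give no expected mortality, no ICC and no design effect. The SORTED C Statistical analysis section says only that analyses will be mainly descriptive, with 95% intervals where appropriate.

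**The concern.** The two sections do not use the same sampling model. The precision claim treats the 400 as independent patients. The sampling section collects them in groups of about 20 per practice. Patients of one practice may share features that bear on survival, such as the area served or the number of care-home residents on the list. Care-home residents are excluded from SORTED A, and the SORTED C text states no such exclusion (Figure 1, the search flow chart, is not visible). That makes some between-practice variation plausible, but it does not give its size.

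The wording is also one-sided. A bound of this kind takes the worst case over mortality, since the half-width peaks at 50%, but the best case over clustering, namely none.

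What is at stake is the planning of SORTED II. The stated aim of SORTED C is to supply the data for that sample size calculation. If patients are correlated within practices and the interval is computed as if they were not, the range of event rates considered for the definitive trial will be too narrow.

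**Working it through.** **Inputs from the protocol article.** n = 400; 95% confidence; target half-width 5 points (Sample size). 20 practices (Sampling and participants), so m = 400/20 = 20 patients per practice.

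**Inputs assumed, because the article gives none.** Mortality p of 0.5, 0.4 and 0.3; ICC of 0.005, 0.01 and 0.02.

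**Step 1: reproduce the stated figure.** For independent patients the half-width is 1.96 × √(p(1−p)/n). At p = 0.5 this is 1.96 × √(0.25/400) = 1.96 × 0.025 = 0.0490, or ±4.90 points. The stated bound reproduces; 385 patients would be enough for it. A Wilson interval gives ±4.88. An exact (Clopper-Pearson) interval gives ±5.01, already at the limit without any clustering.

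**Step 2: how much variance inflation the bound tolerates.** The largest design effect that keeps ±5 points is (5/half-width)². With design effect = 1 + (m−1) × ICC = 1 + 19 × ICC, the largest tolerable ICC is (design effect − 1)/19.

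- p = 0.5: (5/4.90)² = 1.041; ICC = 0.041/19 = 0.0022
- p = 0.4: (5/4.80)² = 1.085; ICC = 0.085/19 = 0.0045
- p = 0.3: (5/4.49)² = 1.240; ICC = 0.240/19 = 0.0126

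At lower mortality the tolerance grows: about 0.020 at p = 0.25 and 0.033 at p = 0.20.

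**Step 3: half-widths over the assumed range.** Multiply the independent half-width by √(design effect). Effective n is 400/design effect.

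| ICC | Design effect | Effective n | p = 0.5 | p = 0.4 | p = 0.3 |
|---|---|---|---|---|---|
| 0 | 1.000 | 400 | ±4.90 | ±4.80 | ±4.49 |
| 0.005 | 1.095 | 365 | ±5.13 | ±5.02 | ±4.70 |
| 0.01 | 1.190 | 336 | ±5.35 | ±5.24 | ±4.90 |
| 0.02 | 1.380 | 290 | ±5.76 | ±5.64 | ±5.28 |

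**Step 4: unequal practices.** With a coefficient of variation CV in practice size, the design effect becomes 1 + ((CV² + 1) × m − 1) × ICC. For an assumed CV of 0.5 and ICC of 0.01 this is 1 + (1.25 × 20 − 1) × 0.01 = 1.24. The half-width at p = 0.5 is then ±5.46 rather than ±5.35, a small addition.

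**The case against.** The strongest reply has four parts.

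- **The arithmetic is correct.** This stands. Nothing in the Sample size section is miscalculated; the fault is an assumption left unsaid.
- **Failure of the bound cannot be shown.** This also stands. A reader might infer that the design does not deliver ±5%. The documents do not support that, because it depends on an ICC and a mortality that they do not give. At 30% mortality and an ICC of 0.01 the half-width is ±4.90, inside the bound. The very low break point of 0.0022 applies only if mortality is 50%.
- **The choice of variance estimator belongs in an analysis plan that is not shown.** This stands as far as it goes. The article neither states nor rules out a clustered variance, and its silence is not a fault. But an analysis plan can only change how the interval is computed. It cannot make good a precision figure promised without conditions for patients sampled through practices.
- **The consequence is small.** This is largely right. SORTED C is descriptive, it tests no hypothesis, and no decision threshold hangs on ±5%. At 50% mortality and an ICC of 0.005 to 0.02 the bound is exceeded by about 0.1 to 0.8 points. The effect on a SORTED II sample size has not been worked out here.

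**Conclusion.** The concern holds in a limited form. The ±5% bound is correct if the 400 patients are independent. It is not secured by a design that samples them through about 20 practices. At 50% mortality it tolerates a variance inflation of only 4.1%. Over an assumed ICC of 0.005 to 0.02 the half-width runs from ±5.1 to ±5.8 points at 50% mortality and from ±4.7 to ±5.3 at 30%, so in part of that range the bound survives. All ICC and mortality values are assumptions. The cluster size of 20 follows from the article's own figures.

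The point is worth correcting because the bound is the sole stated reason for 400 patients and the estimate goes directly into the planning of SORTED II.

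**What to change.** Restate the precision along these lines: a half-width of 4.9 points at worst if patients are independent, and somewhat wider if mortality varies between practices. Give the ICC and the mortality assumed for the second part, labelled as assumptions.

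Compute the mortality and survival intervals with a practice-level clustered variance, or by bootstrapping whole practices, before they are carried into the SORTED II power calculation. Reporting the observed ICC alongside would let readers judge the assumption.

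The cost is one sentence, a little more analysis work and a slightly less favourable stated figure. With only 20 practices, a clustered interval based on a t distribution with 19 degrees of freedom would be wider again: at p = 0.5 and ICC 0.01, 2.093 × 0.025 × √1.19 = 0.0571, or ±5.7 points. No extra patients are needed unless the sponsor wants to keep ±5 points as a firm bound. In that case, at p = 0.5, an ICC of 0.01 would call for about 385 × 1.19 = 459 patients (23 practices of 20).

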#### Sampling and participants

To identify patients for inclusion in the cohort study, the general practice will perform a database search of patient electronic records (Figure 1), which simultaneously identifies patients for SORTED A and C. Based on the information collected in the feasibility work and using an average practice list size of 7,000, we estimate that we need to recruit 20 general practices to achieve a sample size of at least 400 patients. In Northumberland, Tyne and Wear there are approximately 300 general practices of which 65 are GP research sites. The Primary Care Research Network staff will identify 20 practices to approach and will mail out the study literature. We do not anticipate a problem recruiting general practices to participate but if we cannot achieve our cohort of 400 patients from the first 20 general practices recruited, we will approach further practices.

